### Ethical Considerations

This study involved human participants and is covered by French law 2012-300 of 5 March, 2012, known as the Jardé Law, as category 3 research involving the human person, which provides for the analysis of anonymized personal medical data previously collected during routine care. The sponsor and the person directing and supervising the research undertaken ensured that this research was carried out in accordance with the Jardé Law and the Declaration of Helsinki in its latest version.

The study protocol and related participant documents were reviewed and approved by the Comité de Protection des Personnes Sud-Est I (South-East Ethics Committee for the Protection of Persons; October 11, 2021), together with 3 substantial modifications along the course of the study carried out between November 1, 2021, and July 31, 2023. In addition, an ancillary qualitative study has been reviewed and approved by the Comité de Protection des Personnes Sud-Est I (South-East Ethics Committee for the Protection of Persons; May 9, 2022).

The controller and processor of data recorded during this research was the Centre Hospitalier de Cayenne (Cayenne Hospital Center) in accordance with the French Data Protection Act 78-17 of 6 January, 1978, amended by law 2004-801 of 6 August, 2004, and the European Union regulation (EU 2016/679), titled the General Data Protection Regulation.

This research falls within the scope of the Reference Methodology (MR-003). The Centre Hospitalier de Cayenne has signed an undertaking to comply with the Reference Methodology and has a certificate of compliance number 2215826 version 0 from November 20, 2019 (certificate renewed on December 21, 2021, under the number 2224668 version 0). A privacy impact assessment was carried out in accordance with MR-003.

This research was registered on ClinicalTrials.gov under the national clinical trial NCT05174234 and has ID-RCB (National Identifier generated by the French National Medicines Agency) number 2021-A02185-36.

Before the start of recruitment, agreements were signed with all participating centers as well as with relay points to facilitate recruitment by general practitioners, associations, and NGOs.

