### Study Populations and Inclusion Criteria

For the quantitative epidemiological and biographical component, participants were included in 3 groups: a general population group, a group of people living with HIV, and a group of people living with HBV.

The inclusion criteria for all groups were as follows: being born in Haiti (regardless of current nationality), having been in French Guiana for >3 months, being aged between 18 and 60 years, and having no objection to participate in the study. For the group of people living with HIV, the inclusion criteria were as follows: living with HIV and having a diagnosis dating back >3 months (whatever their status with regard to hepatitis B and C), as well as being followed up on by one of the study’s partner physicians at the hospitals in Cayenne, Kourou, or Saint-Laurent-du-Maroni; in outpatient care; or by a partner association. For the group of people living with chronic hepatitis B, the inclusion criteria were living with a chronic HBV infection and having been diagnosed for >3 months (not coinfected with HIV), as well as being followed up on by one of the study’s partner physicians in the hospitals of Cayenne, Kourou, or Saint-Laurent-du-Maroni; in outpatient care; or by a partner NGO.

For the general Haitian population group (not known to live with HIV or HBV), the inclusion criteria were declaring that they were not infected with either HIV or HBV, being under the care of one of the study’s partner physicians, or being recruited in the public space of one of the cities targeted by the study (Cayenne, Matoury, Rémire-Montjoly, Macouria, Kourou, Montsinéry-Tonnegrande, Sinnamary, Maripasoula, Saint-Laurent-du-Maroni, or Mana). Exclusion criteria were being unable to answer the interviewer in French or Haitian Creole; being under guardianship, tutelage, or legal protection; and having already answered the study questionnaire.

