### Participant Enrollment, Sampling Approaches, and Monitoring

For the quantitative aspects of the study, sampling of the Haitian population in French Guiana—little explored, partially hidden (living in informal settlements and without papers), and rapidly evolving—was carried out by combining several methods. Recruitment sites were chosen on a nonprobabilistic and reasoned basis. Locations were selected based on literature analysis, census data, knowledge of the peer community workers, knowledge of partner NGOs, and accessibility and safety. These criteria are listed in Figure 1. Finally, partner hospital departments, outpatient centers (health care access offices, French Red Cross prevention and health centers, and primary care centers), and general practitioners were identified. The hospital services selected were those that limited bias on morbidity (particularly chronic diseases). The medical departments selected for participant screening and enrollment were maternity, pediatrics, dermatology, and the emergency room. In view of the enrollment sites mentioned, an oversampling of women was expected and judged as acceptable.

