**Figure 1 figure1:**
[figure not shown]
Selection criteria for mapping and choosing locations for recruitment for the Parcours d’Haïti study between 2021 and 2023. NGO: nongovernmental organization.

At the recruitment sites, random recruitment was carried out—all people meeting the inclusion criteria were invited to take part in the study. Recruitment was halted once we reached a reasonable number of participants from a statistical power perspective and representativity of the study populations.

To improve the representativeness of the sample, additional recruitment using the snowball method was planned among eligible health and social care professionals and resource persons. Each volunteer participant received 8 cards with an alphanumeric code to be distributed to eligible people within their circle. Those who received a card and wished to participate were able to contact the peer investigators to schedule an interview according to their availability. The entire protocol was explained to them, and they were able to ask any questions they wished before agreeing to take part. This method was used to improve the quality of the sample and minimize selection bias in terms of care and social support as well as insecurity.

For the qualitative components, the samples were chosen based on predefined inclusion criteria, developed previously, to represent the different profiles of stakeholders and individuals. Sampling was stopped for each component when data saturation in the answers was reached.

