### Assumptions and Hypothetical Study Outcomes

#### Quantitative and Biographical Data

In comparison with the results found in the literature, and particularly of the ANRS Parcours 2012 to 2013 study conducted in Paris area, we hypothesize that the study will reveal difficult living conditions after arrival in French Guiana and that these conditions will last for a long time. We will try to confirm that the departures from Haiti were precipitated by historical events and that the routes are more or less complex depending on the path taken. We hypothesize that migratory routes vary according to migration periods. We hypothesize that access to a residence permit is burdensome and that this is a factor negatively impacting the health of people arriving on the Guianese territory. We presume that access to formal housing is very limited and determined by the level of education and knowing someone in French Guiana previously. We hypothesize that relationships are determined by social conditions but that motherhood in women is more determined by age and social representations even when living conditions are precarious. We hypothesize that many people do not have the health coverage to which they are entitled and that health care services, although available, are not necessarily accessible (for reasons that include transport, health coverage, health literacy, and possible discrimination). We will also try to confirm the hypothesis that having contacts with NGOs and social services improves access to care compared to those who have not benefited from this support. We also make the assumptions that people from Haiti experience high levels of food insecurity after arriving in French Guiana and that many people are isolated.

We also hypothesize that the mental health of Haitians living in French Guiana is impaired when living conditions are precarious, violence has occurred, or relatives are separated.

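### The hypothesis that NGO and social-service contact improves access to care is tested in a sample partly recruited through NGOs and care sites, so enrolment depends on both exposure and outcome

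*Protocol article*

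**What the plan says.** Under Assumptions and Hypothetical Study Outcomes (Quantitative and Biographical Data), the study sets out to confirm that "having contacts with NGOs and social services improves access to care compared to those who have not benefited from this support". Study Objectives lists health insurance coverage, access to care and contacts with medico-social structures among the secondary objectives.

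The routes into the quantitative sample are described in several places:

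- **Ethical Considerations:** "agreements were signed with all participating centers as well as with relay points to facilitate recruitment by general practitioners, associations, and NGOs".
- **Participant Enrollment, Sampling Approaches, and Monitoring:** enrolment sites include partner hospital departments and "outpatient centers (health care access offices, French Red Cross prevention and health centers, and primary care centers), and general practitioners". Partner NGOs' knowledge is one of several inputs to the choice of locations.
- **Study Populations and Inclusion Criteria:** HBV participants must be followed by a partner physician at one of three hospitals, "in outpatient care; or by a partner NGO". The HIV criterion is parallel, with a partner association. The general-population group could enter under a partner physician or in the public space of ten named towns.
- **Snowball supplement** (text following Figure 1): "additional recruitment using the snowball method was planned among eligible health and social care professionals and resource persons". Its stated purpose is to "minimize selection bias in terms of care and social support as well as insecurity".

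Statistical Analysis of Quantitative and Biographical Data plans discrete-time logistic regression for yearly indicators and Poisson regression with robust variance for indicators at interview. Limitations accepts that selection bias cannot be excluded, without linking it to this hypothesis.

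**The concern.** The hypothesis compares people with and without NGO or social-service contact on their access to care. NGO relays make people with contact more likely to enrol, and care sites make people with access more likely to enrol. Restricting attention to those enrolled therefore conditions on a common effect of exposure and outcome. That can change an association, or create one where none exists in the population.

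Two safeguards are stated, and neither clearly meets this problem. Hospital services were chosen to limit bias on morbidity, which is a different bias. The snowball is aimed at the right bias, but it is planned among health and social care professionals and resource persons, who are themselves linked to the services under study, so it may not correct it.

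What is at stake is the described level of coverage, access and contact, and a causal-sounding conclusion about NGO support. The analysis section says the work on support and care structures should identify levers and care itineraries to develop, and Expected Follow-up says the results go to social support and care actors.

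**Working it through.** **1. The plan's own figures.** Sample Size: n = z²·p(1−p)/d² = 1.96² × 0.25 / 0.05² = 384.16, matching the stated 384. The targets are 400 HIV, 400 HBV and 1600 general population. The two patient groups are (400 + 400)/2400 = one third of the planned sample. None of these figures is in dispute.

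**2. Selection model.** The article gives no share by route, so all inputs here are assumptions: 40% of the population have contact (E = 1) and 50% have access (D = 1), independently (true OR 1.0). A person is sampled with probability

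s(E,D) = 1 − (1 − base)(1 − a·E)(1 − b·D),

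where base is public-space sampling, a the NGO route and b the care-site route. The sample OR equals the true OR multiplied by s11·s00/(s10·s01).

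| base / a / b | s00 | s10 = s01 | s11 | Sample OR | Sample RR |
|---|---|---|---|---|---|
| 5 / 5 / 5% | 0.05 | 0.0975 | 0.1426 | 0.75 | 0.90 |
| 5 / 10 / 10% | 0.05 | 0.145 | 0.2305 | 0.55 | 0.83 |
| 2 / 10 / 10% | 0.02 | 0.118 | 0.2062 | 0.30 | 0.74 |

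Independent routes push the association downward, against the study's hypothesis.

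**3. Upward case.** Let base be 5% and suppose only people with both contact and access have extra sampling of 5 or 10 points, for example when an NGO refers someone to an enrolling care site. Then OR = 0.10/0.05 = 2.0 or 0.15/0.05 = 3.0 (RR 1.33 or 1.50).

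**4. No distortion of a true null.** If selection acts on only one of the two variables, or the two effects multiply exactly, the OR stays at 1.0.

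**5. A real effect.** Take access of 60% with contact and 40% without (OR 2.25, RR 1.50). Under the three rows above, the OR becomes 1.69, 1.23 and 0.67 (RR 1.22, 1.07, 0.91). If selection acts on the outcome alone (base 5%, care route 10%), the OR stays at 2.25. The RR, which the Poisson model estimates, does not: 0.6×0.145/(0.6×0.145 + 0.4×0.05) = 0.813 against 0.4×0.145/(0.4×0.145 + 0.6×0.05) = 0.659, giving 1.23.

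**6. Descriptive levels.** In the 5/10/10% row, the sampled cells are 0.2×0.2305 = 0.0461 (both), 0.2×0.145 = 0.0290 (contact only), 0.3×0.145 = 0.0435 (access only) and 0.3×0.05 = 0.0150 (neither), in total 0.1336. Access appears as 0.0896/0.1336 = 67% instead of 50%, and contact as 0.0751/0.1336 = 56% instead of 40%.

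**The case against.** The strongest reply is that the sample was not drawn only from NGOs and care sites. The general-population group, 1600 of 2400 planned, could also be recruited in public space. Limitations admits selection bias, the snowball is aimed at selection on care and social support, and the yearly grid lets contact precede access. The article names model families, not analysis samples, so handling of recruitment route may sit in a full protocol or analysis plan that is not shown.

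Much of this stands, and it rules out several stronger readings that a reader might infer:

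- *Everyone was recruited through the services under study.* The public-space route contradicts this.
- *All groups and routes are pooled for this hypothesis.* The article does not say so.
- *Access is met by definition at a care site.* The outcome is not defined in the text shown. Being met in an emergency room or a health care access office does not settle coverage, refusal of care or earlier access, so access is enriched there rather than guaranteed.
- *The snowball worsens the bias.* Cards went to eligible people in volunteers' circles, whose own care status is unknown. The text supports only doubt that it corrects the bias.
- *The study will falsely confirm its hypothesis.* Independent routes bias the other way, and an upward bias needs over-sampling of people with both. That is plausible, because French Red Cross centres are enrolment sites and are also credited with screening and mediation, so one encounter might count as both. This is inference, not stated.

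The model in the working is also a single cross-section. Selection on status at interview need not carry over at the same size to earlier person-years in the discrete-time models.

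What the reply does not remove is the mismatch itself. The hypothesis is worded causally, enrolment depends on both its variables, and for the patient groups follow-up is an entry condition. Ordering events in time does not undo selection at enrolment, and the general caveat does not reach this result.

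**Conclusion.** The concern holds in limited form. The sample is partly selected on both NGO contact and being in care, and for one third of the planned participants one or the other is required for eligibility. Described levels of access and contact are likely to be inflated, and their association can be distorted either way. The illustrative range under a true null is OR 0.30 to 0.75 with independent routes and 2.0 to 3.0 with joint over-sampling. These values rest wholly on assumed sampling fractions and prevalences. Because the share by route is not given, neither size nor sign can be determined, and the documents do not support saying that the findings would be artefacts. The point concerns secondary objectives and one stated hypothesis, not the primary objective, but it should be dealt with before results on NGO support are used.

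**What to change.** For health coverage, access to care, structures encountered and this hypothesis:

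1. Analyse the general-population group separately from the HIV and HBV groups.
2. Report results by recruitment route (public space, care site, NGO, snowball) where route or interview site was recorded, and add an analysis restricted to public-space recruits. The sponsor should verify what was recorded: the article mentions codes on the snowball cards and verification of inclusion group, but no route variable for everyone.
3. Do not count the recruitment encounter itself as contact or access. Add a sensitivity analysis limited to years before the interview year. This should not replace the main analysis, because people are eligible after more than 3 months in the territory and recent arrivals would lose genuine contacts.
4. Word the result as an association rather than as an improvement.

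The analyses had not begun at submission, so no new data collection is needed if route can be recovered. The cost is precision. By the plan's own formula at 50%, the margin is 1.96×√(0.25/1600) = 2.45 points with 1600 people. If, as an assumption, 400 of them came from public space, it would be 1.96×√(0.25/400) = 4.9 points. The public-space subset is less selected but not free of selection, because locations were chosen non-probabilistically and partly on partner NGOs' knowledge. It should be read alongside the other routes, not as a clean reference.

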## Methods

### Study Objectives

From a quantitative perspective, using notably a biographical approach, the main objective of this study was to evaluate the frequency of sexual behavior exposing people from Haiti to the risk of HIV infection after their arrival in French Guiana and its association with their living conditions. Secondary objectives consisted in describing migration routes, living conditions, access to health insurance coverage and health care, contacts with medico-social structures, social support, general state of health, mental health, and levels of food insecurity after arrival in French Guiana. With regard to sexual and reproductive health and rights, the objectives were to study the delay in first screening for sexually transmitted infections (STIs), as well as the factors associated with earlier screening; study the delay in entry into care and retention in care for people living with HIV or HBV and their determinants; and investigate the use of birth control methods, the frequency of wanted and unwanted pregnancies, and the use of abortion. With regard to emotional life, the objectives were to describe the relational and sexual life.

From a qualitative exploratory perspective, the objectives were to investigate and describe the social representations of HIV and HBV infections and their impact on the use of prevention and biomedical and traditional care. In addition, representations of the Guianese health care system and its prevention services were explored, as well as an anthropological understanding of representations of the body and illness in relation to the ethnomedicinal conceptions of people of Haitian origin living in French Guiana. Finally, another objective was to explore the obstacles to and facilitators of accessing mental health care and understand the mental health problems encountered and the responses provided to migrants in French Guiana from the point of view of health professionals, social workers, and local nongovernmental organizations (NGOs). From a phylogenetic perspective, we aimed to describe the distribution of clades of the Pol gene in the viruses of people living with HIV from Haiti.

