The cross-sectional epidemiological questionnaire collected data related to arrival and stay in French Guiana, history of administrative procedures to stay for medical reasons, sexual and reproductive health, coerced or transactional relationships over the lifetime, use of birth control methods before and after arrival in French Guiana, use of HIV screening tests, general health status, mental health status (4-item Patient Health Questionnaire scale and the psychotrauma scale of the Post-Traumatic Stress Disorder-8), substance use (Alcohol Use Disorders Identification Test–Consumption scale), health insurance coverage, refusal of care experience, food insecurity and hunger, and use of nonallopathic medicine [27-29]. For the groups of participants living with HIV or HBV, 2 short complementary modules were completed in the cross-sectional questionnaire, follow-up and treatment histories were also collected biographically, and medical questionnaires containing routine biological and medical information were completed (Multimedia Appendix 1). Cross-sectional questionnaire data were collected using the ODK Collect software (Get ODK Inc) on tablets. Transversal data entry was conducted offline, and then data were extracted manually using an R script (R Foundation for Statistical Computing) to transform instances into a CSV database [30]. Biographical data were collected on paper biographical grids and then coded using a dictionary of variables and corresponding labels.

The second main tool used was a biographical grid, with the following information collected retrospectively year after year over the lifetime: residential history, administrative history, health coverage, history of professional activities, sources of income, history of relationships, pregnancies and children, history of screening tests for HIV, HBV and cervical cancer screening, history of illnesses and hospitalizations, health or social support structures encountered since arrival in French Guiana, perceived annual well-being, hunger, and significant events. For the groups of participants living with HIV or HBV, follow-up and treatment histories were also collected biographically. The biographical grid data were then entered into Ennov Clinical by a clinical study technician. The decision to freeze the quantitative databases was taken on March 13, 2024, once the data entry and control processes had been completed. The controls continued until June 7, 2024.

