#### Statistical Analysis of Quantitative and Biographical Data

With regard to the statistical analysis of quantitative information, the major indicators will be described using percentages as well as means or medians with their SDs or IQRs depending on their distribution. Analytical work will be carried out with a biographical and social epidemiology approach using the tools of epidemiological analysis to study the associations between behaviors and health indicators and social determinants. Factors associated with biographical key indicators will be analyzed year after year using discrete-time logistic regression models that take into account time and the values of indicators collected in the biographical grid year after year [31]. Factors associated with indicators collected at the time of the study will be analyzed using Poisson regression with robust variance. The Stata software (StataCorp) will be used to conduct the analyses.

An analysis of the participants’ support and care structures will be carried out based on specific questions that will be analyzed through clustering and a bipartite network approach using methods derived from graph theory. These analyses will provide a better understanding of the levers and care itineraries that can be developed. The R software will be used for these analyses (*tidyverse* and *tidygraph* packages).

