During these years, people may be exposed to situations of sexual vulnerability and to unwanted sexuality and transactional, paid, or even forced sex, exposing them to a greater risk of acquisition of HIV or STIs and psychological trauma. In terms of sexual health, we hypothesize that, regardless of the participant group, a large proportion of the population has been exposed to sexual violence and transactional relationships and that these phenomena particularly concern women. Finally, we hypothesize that the use of contraception is low and that recourse to abortion is very limited.

Concerning the follow-up of people living with HIV and people living with HBV, we hypothesize that Haitian populations in French Guiana use screening relatively early and that those diagnosed with HIV enter care relatively early, in line with the screening and mediation services available in the region, notably through the French Red Cross. We also think that impaired social conditions, social isolation, and low health literacy are associated with a delay in screening. A catch-up certainly exists for women during pregnancy. It is likely that periods of disruption of care are closely linked to the social situation of the people concerned, which changes from year to year. The biographical approach will enable us to confirm the hypothesis that, in the years during which a disruption in care occurred, the person faced social or administrative difficulties more often. In addition, we assume that periods of loss to follow-up are more frequent among people living with HBV, linked to an incomplete understanding of the disease, the absence of therapeutic indications for a large proportion of people living with HBV, prolonged follow-up intervals, and a lower civil society investment than that in people living with HIV. With regard to people living with HIV, we hypothesize that they will report unprotected sex in the years following their infection.

Finally, we hypothesize that conducting a long interview focusing on health issues is likely to contribute to respondents’ access to and use of health care.

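### The care-disruption hypothesis reads as a comparison within a person, but the yearly model as described mixes within-person change with stable differences between people and could confirm it without any within-person link

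*Protocol article*

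**What the plan says.** The Study Objectives include, as a secondary aim, to "study the delay in entry into care and retention in care for people living with HIV or HBV and their determinants". Under Assumptions and Hypothetical Study Outcomes (Quantitative and Biographical Data), periods of disrupted care are expected to be "closely linked to the social situation of the people concerned, which changes from year to year". The next sentence begins "The biographical approach will enable us to confirm the hypothesis that" and continues: "in the years during which a disruption in care occurred, the person faced social or administrative difficulties more often". The comparator for the last two words is not written out.

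For the analysis, Statistical Analysis of Quantitative and Biographical Data states: "Factors associated with biographical key indicators will be analyzed year after year using discrete-time logistic regression models". These models are to "take into account time and the values of indicators collected in the biographical grid year after year". No other model is named for yearly data. The section neither mentions nor excludes a person-level term, and it does not refer to the disruption hypothesis by name. Data Collection Tools says that for the HIV and HBV groups "follow-up and treatment histories were also collected biographically", so yearly data for a within-person comparison should exist.

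**The concern.** The hypothesis is about the person in particular years, and it follows a sentence about a situation that moves over time. A matching estimate would ask whether the same person has more difficulties in disrupted years than in undisrupted ones.

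A discrete-time logistic model on pooled person-years answers a blend of two questions. One is whether disruption accompanies a change in a person's situation. The other is whether people who are lastingly precarious are also lastingly less well retained. Only the first is the hypothesis. Person-clustered standard errors alter the precision, not the estimate. A random intercept assumes the person effect is independent of difficulty, which is the point in doubt.

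The distinction matters because Expected Follow-up intends the results to inform measures against loss to follow-up. Responding when someone's situation worsens is a different measure from supporting a stable high-risk group, and a blended odds ratio cannot tell them apart.

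**Working it through.** **The plan's own figures.** The article gives no figure on this point. Its one calculated number is reproduced, 1.96² × 0.5 × 0.5 / 0.05² = 384.16 (stated: 384), but it concerns the precision of a proportion. Only the target of 400 people per infection group (Sample Size) is carried over. Everything else below is assumed, because the article gives no disruption rate, number of follow-up years or degree of lasting difference between people.

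**Step 1: odds ratio by hand with no within-person link.** Suppose 30% of people are chronically precarious. They have difficulty in a share a₁ of years and disruption in a share d₁; the others have a₀ and d₀. Within each type, difficulty and disruption are independent from year to year. Then:

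- P(disruption | difficulty) = (0.3·a₁·d₁ + 0.7·a₀·d₀) / (0.3·a₁ + 0.7·a₀)
- P(disruption | no difficulty) = (0.3·(1−a₁)·d₁ + 0.7·(1−a₀)·d₀) / (0.3·(1−a₁) + 0.7·(1−a₀))

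| Difficulty a₁/a₀ | Disruption d₁/d₀ | With difficulty | Without difficulty | Pooled OR |
|---|---|---|---|---|
| 70%/20% | 15%/5% | 0.0385/0.35 = 0.110 | 0.0415/0.65 = 0.064 | 1.81 |
| 60%/25% | 12%/5% | 0.03035/0.355 = 0.085 | 0.04065/0.645 = 0.063 | 1.39 |
| 50%/30% | 12%/6% | 0.0306/0.36 = 0.085 | 0.0474/0.64 = 0.074 | 1.16 |

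**Step 2: simulation of the same scenarios** (400 people, 8 years each, 200 runs, clustered errors, no other covariates).

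- Pooled model: OR 1.81 / 1.38 / 1.16, with p<0.05 in 99.5% / 62% / 19.5% of runs.
- Random intercept: OR still 1.71 / 1.34 / 1.15.
- Person mean and yearly deviation added: within-person OR 1.00 / 0.98 / 1.00, with p<0.05 in 2.5% / 6.5% / 6.5%.

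**Step 3: a different data-generating model.** Here a continuous stable trait has SD 1 on the logit of disruption and a varying correlation with chronic difficulty. There is again no within-person effect (60 runs each, so the rates are approximate).

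| Correlation | Pooled OR | Falsely confirmed | Person-conditional OR | Rejected |
|---|---|---|---|---|
| 0 | 1.01 | 0% | 1.01 | 3% |
| 0.3 | 1.24 | 52% | 1.01 | 3% |
| 0.5 | 1.50 | 95% | 1.02 | 3% |
| 0.8 | 1.83 | 100% | 0.99 | 0% |

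With a weaker trait (SD 0.5, correlation 0.5) the pooled OR is 1.23, falsely confirmed in 43% of runs. Modelling only the first disruption does not remove the problem: at correlations 0.3 / 0.5 / 0.8 the pooled OR is 1.18 / 1.37 / 1.69, falsely confirmed in 22% / 63% / 97% (200 runs).

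**Step 4: when a within-person effect exists.** With a true within-person OR of 1.5, the first scenario of step 1 gives 2.69 pooled and 1.49 from the deviation term (power about 75%). The step 3 model at correlation 0.5 gives 2.03 pooled and 1.48 conditional.

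**Step 5: weakness of the within-person estimate.** Suppose disruption raises the odds of difficulty in the next year two- or threefold (first scenario, 300 runs). The deviation term then gives 0.91 or 0.88 when the truth is 1, and 1.37 or 1.31 when the truth is 1.5. Power in the latter case falls to 54% or 42%.

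**The case against.** The best counter-argument is that one sentence in a condensed article names a model family and no more. Parameterisation, covariates and the treatment of repeated years usually sit in the full protocol or analysis plan. A reader might infer that a person-level term has been ruled out; the article does not say so. This part stands, and the point is not that detail is missing. It is that the article makes a confirmatory statement and describes a model which, followed as described, cannot support that statement separately.

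Second, the comparator is implied. A comparison of disrupted with undisrupted person-years over everyone also fits the words, and on that reading nothing conflicts. This stands as a possible reading, though the reference to the person and to a situation that varies over time makes the within-person reading the more natural one.

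Third, the sizes are assumed and come from models without covariates. The article plans multivariable work and records residence, administrative status, coverage and income each year. Adjustment may shrink the bias, but it cannot be counted on to remove every stable difference.

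Fourth, the remedy has a weakness of its own, shown in step 5. Feedback is plausible here, since the questionnaire records administrative procedures to stay on medical grounds. This stands and belongs in the fix.

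Finally, this is one of many expectations in a Discussion section, tied to a secondary objective and with no decision rule attached. That limits the stakes.

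**Conclusion.** The point holds in a limited form. The model as described does not isolate the within-person contrast that the hypothesis most naturally expresses, so it could confirm the hypothesis when there is no such link. Under assumed scenarios without a within-person effect the pooled odds ratio is about 1.16 to 1.83. At SD 1 and zero correlation between the stable trait and chronic difficulty it is 1.01, with no excess of false confirmation.

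Two stronger readings are tempting and are not supported. One is that the model compares only different people; in fact it blends both contrasts. The other is that it would confirm the hypothesis falsely. That happens only if stable traits drive both difficulty and disruption and are not captured by adjustment, and the article gives no data on how strong such traits are. No printed figure is wrong.

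The change is worth making because it is cheap, the data are already collected, and the article says analyses had not begun at submission.

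**What to change.** For this hypothesis:

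- Keep every year since diagnosis, including years after a return to care.
- Fit the planned discrete-time logistic model with two terms for each difficulty indicator: the person's own mean and the yearly deviation from it. Include time since diagnosis and use person-clustered errors.
- Base the within-person conclusion on the deviation term and report the between-person term separately.
- Use logistic regression conditional on the person as a check.
- Add a sensitivity analysis for feedback, for example adjusting for the previous year's disruption. Read it as an indication: feedback also acts through later years that enter the person's mean, and a lag term does not take that out. If disruption is often followed by new difficulty, say that the within-person estimate may be too low.

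If the full plan already contains such a split, one sentence in the article's analysis section settles the matter. If a within-person analysis is not wanted, word the hypothesis and the result only as an association across person-years.

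The cost is some analysis wording and simple derived variables, with no new data. The downsides to state are lower precision, a conditional check that uses only people with both disrupted and undisrupted years, and the assumption behind both within-person estimates that disruption does not alter later difficulties.
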